### Explanation for the choice of comparators {6b}

According to international guidelines and the WHO recommendation, high-risk populations received benefits from influenza vaccination if it is undertaken prior each influenza season. To ensure the application of ethical principles of equity and benefit, this study uses a hospital-based cluster design where participants allocated to control usual care arm are not denied the right to receive influenza vaccine. However, in previous reports [15] and our pilot phase [17], voluntary influenza vaccination rates were very low (< 1%) in China. Thus, the control arm is interpreted to be generally vaccination-free.

### Criteria for discontinuing or modifying allocated interventions {11b}

In the intervention group, only participants who provide consent to be vaccinated will receive influenza vaccine prior to hospital discharge. Participants who refuse the vaccine but consent to follow-up are still included in the intension-to-treat (ITT) analysis. The trial uses a one-off intervention, and no alternate or modified intervention will be implemented. However, participants have the right to discontinue their participation in the study at any time during follow-up, and an investigator has the right to modify receipt of the intervention if it is deemed in the best interests of the participant or guided by local policy.

### Strategies to improve adherence to interventions {11c}

A standardized educational curriculum on influenza vaccination in HF patients was developed for participating investigators, with the objective of ensuring that most participants are vaccinated in the intervention group. Moreover, study sites are required to provide screening logs to record the proportion of eligible patients who consent to participate. The study coordinating center will provide feedback to enhance adherence to study protocol.

### Relevant concomitant care permitted or prohibited during the trial {11d}

The treatment of HF is to follow the guidelines of the Chinese Society of Cardiology. There is no modification of background standard of care in both groups, except for the use of influenza vaccination in the intervention group.

### Provisions for post-trial care {30}

No post-trial care or compensation is anticipated.

### Outcomes {12}

The primary outcome is the composite of all-cause death or all-cause hospitalization in influenza season (defined by national CDC) within 1 year after hospital discharge. Hospitalization is defined as clinical manifestations that require admission (for at least 24 h) or emergency room stay (for at least 24 h). Non-influenza season events are unlikely to be attributable to influenza infections. Events beyond the corresponding influenza season are unlikely to be prevented by influenza vaccine. Influenza vaccines are estimated to have protective effects by generating antibodies within 30 days post-vaccination, so events occurring within 30 days after discharge are considered unlikely to be preventable by influenza vaccination. Thus, events that occur in that occur in the non-influenza season or within 30 days after hospital discharge will be excluded from primary outcome analysis.

The secondary outcomes are:All-cause death within 1 year;All-cause hospital re-admission within one year;Composite of all-cause death or all-cause hospitalization within 6 months;All-cause death within 6 months;All-cause hospital re-admissions within 6 months.

Exploratory outcomes included the average number of all-cause hospital readmissions over a 1-year period, which refers to the average number of hospitalizations for any cause over a 1-year period. Another outcome is ILI, defined as ≥ 38 °C, cough or sore throat, within the past 7 days at each follow-up site. Safety outcomes are all-cause and cause specific serious adverse events (SAEs) according to standard definitions until the end of follow-up.

### Participant timeline {13}

The PANDA II study will be undertaken in an interrupted series over three 1-year periods. The time schedule of patient enrollment is between October 1, 2021, and March 31, 2022; October 1, 2022, and March 31, 2023; and October 1, 2023, and March 31, 2024. All patients are followed up over a 12-month period. Thus, the study is due for completion in April 2025. The overall timeline and the milestones are listed in Fig. 1, and the activities for each patient visit are presented in Appendix Table S1.

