**Methods:**

The second Population Assessment of Influenza and Disease Activity (PANDA II) study is a two-arm, parallel-group, county-level hospital-based, cluster randomized controlled trial to determine the benefits and risks of full access to routine free influenza vaccination before hospital discharge, compared to routine limited use of influenza vaccination, on the primary endpoint of death or hospital readmission. Consecutive hospitalized patients at each site are enrolled to a target of 50 participants in each autumn–winter influenza outbreak period (October to March) over 3 consecutive years to reach the required sample size. Patients are centrally followed up at 1, 3, 6, and 12 months after hospital discharge (or death if earlier). Site numbers varied across year according to predicted influenza activity and logistical reasons.

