### Sample size {14}

The sample size for this study was based on the following assumptions:A influenza infection rate of 15% in the background population80% of infected patient will experience the primary endpoint if infected with influenza90% of patients in the intervention group will receive the influenza vaccine, and 10% of patients in the control group received the vaccineinfluenza vaccination has at least 60% protection for influenza infection10% of patients are lost to follow-up at 12 months

According to previous research, the 1-year death or hospital readmission rate for patients with HF is 50 per 100 person-years, after events in the non-influenza season or within 30 days of hospital discharge are excluded [18]. The intra-class correlation coefficient (ICC) for 1-year mortality or HF-specific readmission rates at participating hospitals was 0.03. A sample size of 122 hospitals participating over 3 influenza seasons in which 50 patients are recruited per hospital each season would provide 90% power at a two-tailed significance level of < 0.05. Sample sizes were calculated using PASS 2020 software under the “test for two proportions in a cluster randomized design” module.

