## Trial status

The study has received approval from relevant ethics committees and regulatory bodies at both national and local levels in China. Patient enrollment began on December 1, 2021, and concluded on February 8, 2024. The current protocol is version 3.0 (date: April 30, 2024), and all protocol amendments have been approved by study steering committee and Medical Ethics Committee of Beijing Anzhen Hospital affiliated to Capital Medical University (Research Ethics Review (2021) No.18) and communicated with investigators and DSMB members.

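### The sample size applies vaccine protection to an unreduced 15% infection rate, although entry runs to 31 March, the first 30 days are excluded and protection is limited to one season

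*Protocol article*

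**What the plan says.** - **Entry window.** Participant timeline {13}: "The time schedule of patient enrollment is between October 1, 2021, and March 31, 2022", with the same calendar window in the next two seasons. The article gives no last discharge date tied to the end of the season.
- **Outbreak period.** The abstract's Methods place recruitment "in each autumn–winter influenza outbreak period (October to March) over 3 consecutive years".
- **Counted events.** Outcomes {12} counts death or hospitalization "in influenza season (defined by national CDC) within 1 year after hospital discharge". No season dates are given.
- **Blanking.** The same section removes early events because "events occurring within 30 days after discharge are considered unlikely to be preventable by influenza vaccination".
- **Reach of protection.** It adds: "Events beyond the corresponding influenza season are unlikely to be prevented by influenza vaccine".
- **Planning inputs.** Sample size {14} lists "A influenza infection rate of 15% in the background population", with no time window. It describes its 50 per 100 person-years event rate as already net of off-season and first-30-day events.
- **Actual dates.** Trial status: "Patient enrollment began on December 1, 2021, and concluded on February 8, 2024".

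**The concern.** The planned effect comes entirely from influenza infections that vaccination prevents. By the protocol's own reasoning, these can occur only after day 30 and before the end of the season of enrolment. Patients enter on a rolling basis, so each has a different and shortened stretch of such time. Late entrants may have none, yet they count toward the quota of 50 per site.

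Sample size {14} treats its two main inputs differently. The event rate is stated after the exclusions. The infection rate, to which the 60% protection is applied, is stated for the background population with no reduction for entry date or blanking. If 15% is a season-long figure, the planned difference is too large for the patients the window admits. The Discussion's description of the study as well powered would then rest on an effect that is not available, and a neutral result would be hard to interpret.

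**Working it through.** **1. The plan's own figure.** Inputs from Sample size {14}: infection 15%, protection 60%, coverage 90% v 10%, endpoint risk if infected 80%, control risk 0.50, ICC 0.03, 122 hospitals (61 per arm), 50 patients per hospital per season, 10% loss.

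- Infection by arm: 15 × (1 − 0.6 × 0.1) = 14.1% v 15 × (1 − 0.6 × 0.9) = 6.9%, a difference of 7.2 points.
- Endpoint difference: 7.2 × 0.80 = 5.76 points, i.e. 0.50 v 0.4424.
- Design effect 1 + (m − 1) × 0.03; effective size per arm 61 × m / design effect; normal approximation, two-sided 0.05:

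| m | Design effect | Effective n per arm | Power |
|---|---|---|---|
| 50 | 2.47 | 1235 | 81.8% |
| 45 (after loss) | 2.32 | 1183 | 80.2% |
| 150 (three seasons pooled) | 5.47 | 1673 | 91.6% |
| 135 (pooled, after loss) | 5.02 | 1640 | 91.1% |

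With 50 per cluster, 122 does not give 90%. It does if each of 122 hospitals contributes three seasons, which sits badly with the limit of 60 hospitals a year in Study setting {9}. It also nearly does (89.8%) with no vaccination in controls and no loss. That mismatch is a separate matter and is not evidence for this point. Both cluster readings are carried forward.

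**2. Protectable days.** Let the season start on 1 October and last S days, with discharge on day t. Own-season protectable time is max(0, S − t − 30). For March discharges:

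- Season ends 31 March (S = 182): 1 March + 30 days = 31 March, so none.
- Season ends 30 April (S = 212): 0–30 days.
- Season ends 31 May (S = 243): 31–61 days.

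**3. Share of the season captured.** The documents give no season dates, discharge distribution or weekly activity, so these are illustrations. The peaked variants use a normal activity curve (SD 30 days) peaking between 1 and 29 January.

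- *Even entry, 1 October to 31 March.* S = 182: mean 152² / (2 × 182) = 63.5 days, 34.9%. S = 212: 91 days, 42.9%. S = 243: 122 days, 50.2%. Peaked: 34–50%.
- *Pilot pace from 1 December.* The pilot enrolled 518 patients at 11 hospitals (518/11 = 47 each) from 28 December to 29 January, 33 days. Mean t = 77.5; with S = 182, 182 − 77.5 − 30 = 74.5 days, 41%. Later season ends: 49% and 56%. Peaked: 31–65%.
- *Pilot pace from 1 October.* Mean t = 16.5; with S = 182, 135.5 days, 74%. Later season ends: 78% and 81%. Peaked: 93–99%.

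**4. Effect and power.** If 15% is a season-long rate, infection and difference scale with the share f: infection = 15 × f, difference = 5.76 × f. Control risk is held at 0.50, with 122 clusters:

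| Scenario | f | Infection | Difference (points) | Power, m = 45 | Power, m = 135 |
|---|---|---|---|---|---|
| As planned | 1.00 | 15.0% | 5.8 | 80.2% | 91.1% |
| Even entry, ends 31 March | 0.349 | 5.2% | 2.0 | 16.3% | 20.9% |
| Even entry, ends 31 May | 0.502 | 7.5% | 2.9 | 29.0% | 38.1% |
| Pilot pace from 1 December, low | 0.31 | 4.7% | 1.8 | 13.8% | 17.4% |
| Pilot pace from 1 December, high | 0.65 | 9.8% | 3.7 | 44.5% | 57.4% |
| Pilot pace in October, low | 0.74 | 11.1% | 4.3 | 54.6% | 68.6% |
| Pilot pace in October, high | 0.99 | 14.9% | 5.7 | 79.4% | 90.6% |

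**The case against.** **The season is defined by the national CDC, not as October to March.** This stands. That March discharges have no protectable time is conditional on a 31 March end. A later end narrows the gap, but mid-season entrants still lose exposure.

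**Sites do not fill evenly over six months.** This largely stands. Each stops at 50, must handle a high volume of heart failure patients, and filled in about a month in the pilot. The third season closed on 8 February 2024, so it had no March entrants. A reader might infer from the window that a sixth of patients (30/182) have no protectable time, or a quarter (30/121) with a 1 December start. Those shares need slow, even filling to 31 March and a season ending that day, and nothing shows that this occurred.

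**Late entrants still contribute events.** True. The outcome runs for a year, so the following season counts, and it would be wrong to call these patients structural zeros. However, Outcomes {12} says the vaccine is unlikely to prevent those events, so they add dilution rather than signal.

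**The 15% may already be specific to the window.** Possible. Calling it a full-season rate is an inference, since no window is stated. But a rate for the background population does not read as net of blanking, whereas the event rate beside it is expressly net.

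**Excluding late discharges from the primary analysis would be worse.** This stands. Discharge follows allocation in an open-label trial, vaccine is given in the last 24 hours before discharge, and the stated rule is intention-to-treat in all participants.

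**Conclusion.** The point holds in conditional form. Entry to 31 March, 30-day blanking and same-season protection do not fit an unreduced 15% infection rate. Unless that 15% already describes the period after day 30 within the season of enrolment, the 5.76-point effect and the 90% power are overstated.

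The direction is the same in every scenario, but the size is not fixed by the documents. The captured share is about 35–50% for even entry, 31–65% for pilot-pace filling from 1 December, and 74–99% for pilot-pace filling in October. Only quick October filling with a January peak comes close to the planned effect. Trial status shows that the first season opened on 1 December 2021, so October filling was not available that year. How many patients entered in March is unknown for the first two seasons; none did in the third.

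A reader might conclude that the trial is bound to be neutral, or that entry dates alone would explain a neutral result. The documents do not support that: actual discharge dates, the season dates by region and the window meant by the 15% are not given.

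**What to change.** 1. In Outcomes {12}, give the CDC season dates used, by region and year.
2. In Sample size {14}, state the window to which the 15% refers. Replace it with the infection rate expected in the protectable window, given the actual discharge dates, and restate the difference and power.
3. Keep all enrolled patients as the intention-to-treat primary population.
4. Before unblinding, pre-specify one supportive analysis limited to patients in both arms admitted or discharged at least 31 days before season end. Report vaccination and discharge timing by arm alongside it. Admission date is less open to influence by allocation than discharge date.

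The cost is wording and one extra analysis on recorded dates. Enrolment has ended, so the sample cannot change, and the restated power will probably be less favourable.

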### Sample size {14}

The sample size for this study was based on the following assumptions:A influenza infection rate of 15% in the background population80% of infected patient will experience the primary endpoint if infected with influenza90% of patients in the intervention group will receive the influenza vaccine, and 10% of patients in the control group received the vaccineinfluenza vaccination has at least 60% protection for influenza infection10% of patients are lost to follow-up at 12 months

According to previous research, the 1-year death or hospital readmission rate for patients with HF is 50 per 100 person-years, after events in the non-influenza season or within 30 days of hospital discharge are excluded [18]. The intra-class correlation coefficient (ICC) for 1-year mortality or HF-specific readmission rates at participating hospitals was 0.03. A sample size of 122 hospitals participating over 3 influenza seasons in which 50 patients are recruited per hospital each season would provide 90% power at a two-tailed significance level of < 0.05. Sample sizes were calculated using PASS 2020 software under the “test for two proportions in a cluster randomized design” module.

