## Discussion

The PANDA II study aims to provide direct and reliable evidence on the effectiveness and safety of influenza vaccination in patients with acute HF. It follows the implementation strategy proposed in a pilot study [17], where a 90% vaccination coverage rate (VCR) was achieved in the intervention group, and remained as low as < 1% in the control group as influenza vaccines are not covered by the national immunization program in regions of China [16]. A strength of this trial is the design, which provides an exceptional opportunity to evaluate both efficacy and policy perspectives regarding the protective effect of influenza vaccination in patients with HF.

Another strength of this trial lies in its recruitment strategy, which leverages the existing HF health provider network and ensures the inclusion of consecutive and representative participants. The construction of POV in hospitals during the trial enhances the intervention implementation and site adherence, which can be scaled up into a routine practice should the intervention prove to be effective. Despite encountering logistical challenges associated with the conduct of such a large cluster trial in a range of low resource settings where there are varying levels of trial experience, our research team has implemented centralized monitoring and tracking systems for participating hospitals and patients to ensure data quality. Furthermore, the study faced difficulties due to the COVID-19 pandemic. It can be expected that the outcome event rates will differ according to times of co-circulation the COVID-19 virus and influenza activity was low in the period of quarantine policy in 2021. We did not initiate the study until the influenza activity surveillance reported an ILI + /ILI > 3% at week 38 of 2021. In 2022, a higher mortality rate in patients with HF was observed due to COVID-19 infection, which may dilute the effect of influenza vaccination. However, stratified cluster randomization design is expected to keep the influence balanced between study arms. A sensitivity analysis will be performed to evaluate the impact of COVID-19.

Our study is a well-powered and on schedule to resolve uncertainty over influenza vaccination in an effectiveness-implementation hybrid design, while also providing a model for future preventive strategies in patients. Insights gained from this study will inform and enhance HF management practices in regions where influenza vaccine uptake remains low.

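### Read as a one-year risk, the stated inputs imply an effect of about 2.5 to 3.4 percentage points, which does not give the claimed 90% power; the two proportions behind that claim are not stated

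*Protocol article*

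**What the plan says.** All inputs are in the Sample size section {14} of the protocol article:

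- "A influenza infection rate of 15% in the background" population;
- 80% "of infected patient will experience the primary endpoint if infected with" influenza;
- 90% "of patients in the intervention group will receive the influenza vaccine, and 10% of patients in the control group received" it;
- at least 60% vaccine protection against infection;
- 10% "of patients are lost to follow-up at 12 months".

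The background is given as a rate: "the 1-year death or hospital readmission rate for patients with HF is 50 per 100 person-years", after out-of-season events and events in the first 30 days are removed. On clustering: "The intra-class correlation coefficient (ICC) for 1-year mortality or HF-specific readmission rates at participating hospitals was 0.03". The size is "A sample size of 122 hospitals participating over 3 influenza seasons in which 50 patients are recruited per hospital each season", said to give 90% power at two-sided 5% with a cluster-randomized two-proportion module. No target difference and no control or intervention proportion is given.

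Three other sections matter. Outcomes {12} makes the primary endpoint all-cause death or all-cause hospitalization. Study setting {9} caps randomization at 60 hospitals a year, and hospitals are re-randomized each season. The Discussion concludes: "Our study is a well-powered and on schedule to resolve uncertainty over influenza vaccination".

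**The concern.** The 80% is worded as the absolute risk of the endpoint in an infected patient, not as risk added by infection. Patients with NYHA class III or IV heart failure who escape influenza still die or are readmitted often. Vaccination therefore cannot be credited with every event among the infections it prevents, only with the excess over the risk those patients would have had anyway. The plan supplies both quantities needed to see this, an overall background and a risk if infected, but shows no step that combines them.

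What is at stake is how the result will be read. If the realistic effect is far below what the trial can detect, a non-significant result from a trial described as well powered could be taken as evidence that vaccination does not help.

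**Working it through.** **Infection by arm.** Infection risk = 0.15 x (1 - coverage x 0.60).

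- Control: 0.15 x (1 - 0.10 x 0.60) = 14.1%
- Intervention: 0.15 x (1 - 0.90 x 0.60) = 6.9%
- Difference: 7.2 points

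**Trying to reproduce the 90%.** Counting every event in infected patients as preventable gives 0.072 x 0.80 = 5.76 points (50.0% v 44.24%). With ICC 0.03 that yields about 80% power for 122 hospital-seasons of 45 (50 less 10% loss), and about 91% to 92% for 122 hospitals treated as single clusters of 135 to 150. The stated figure is therefore approached with 5.76 points and the large-cluster layout, but 5.76 treats uninfected patients as having no risk.

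**Effect using excess risk.** Effect = difference in infection x (risk if infected - risk if not infected). The uninfected risk follows from the overall control risk R as (R - 0.141 x 0.80)/0.859.

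- R = 50%: uninfected risk (0.50 - 0.1128)/0.859 = 45.1%; effect 0.072 x (0.80 - 0.451) = 2.51 points, or 50.0% v 47.5%.
- R = 1 - exp(-0.5) = 39.3%: uninfected risk 32.7%; effect 0.072 x (0.80 - 0.327) = 3.41 points.
- If 50% is instead the risk in the uninfected: 0.072 x (0.80 - 0.50) = 2.16 points.

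**Power.** Effective number per arm = (K/2) x m / (1 + (m - 1) x 0.03), for K clusters of m analysed patients. Power = Phi(d/SE - 1.96).

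For K = 122, m = 45, d = 0.0251: 61 x 45/2.32 = 1,183 per arm. SE = sqrt((0.50 x 0.50 + 0.475 x 0.525)/1,183) = 0.0205. Then d/SE = 1.23 and power = 23%.

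| Layout (after 10% loss) | Effective n per arm | Power, R = 50% (2.51 points) | Power, R = 39.3% (3.41 points) | Detectable with 90% power (R = 50%) |
|---|---|---|---|---|
| 122 hospital-seasons of 45 | 1,183 | 23% | 40% | 6.6 points |
| 180 hospital-seasons of 45 (ceiling of 60 a year x 3) | 1,746 | 32% | 55% | 5.5 points |
| 366 hospital-seasons of 45 (122 x 3) | 3,550 | 56% | 84% | 3.8 points |
| 122 hospitals of 135 as single clusters | 1,640 | 30% | 52% | 5.6 points |

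Ignoring loss to follow-up adds one or two points; the highest value is then 86% (3.41 points, 366 hospital-seasons of 50). At 2.51 points, 90% power would need about 858 hospital-seasons of 45. The 366 layout exceeds the yearly ceiling, and the single-cluster layout does not fit re-randomization each season; both are shown for completeness.

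**A shorter time at risk.** Suppose the person-year rate applies only to in-season time after day 30, taken here as about 5/12 year (October to March less 30 days; an assumption). Then R = 1 - exp(-0.5 x 5/12) = 18.8%, uninfected risk is 8.8%, the effect is 0.072 x (0.80 - 0.088) = 5.1 points, and 122 hospital-seasons of 45 give 92%. The result is sensitive to the assumed time:

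- four months: 5.4 points, 98% at 122 hospital-seasons;
- six months: 4.9 points, 84% at 122 and 95% at 180;
- nine months: 4.1 points, 59% at 122, 76% at 180 and 97% at 366.

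**The case against.** The best reply is that the protocol gives a rate, not a proportion, and does not say whether excluded time stays in the denominator. Only in-season time after day 30 can produce a primary event, so a rate applied to about five months is permitted by the text, and the last calculation above shows that it restores roughly 90% at 122 hospital-seasons. This stands. A reader might infer that no reading of the sample size reaches 90%; the document does not support that. The shorter window is nevertheless strained: the text calls the figure a one-year rate and nowhere mentions a five-month conversion.

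Two other stronger readings also fail. One is that the authors used 5.76 points. No effect is printed, and 5.76 gives only 80% at 122 hospital-seasons, so this is an inference from numbers that come close under one layout. The other is that the effect can never exceed 4.2 points. That ceiling sets the risk if infected to 100% with R = 50% (uninfected risk 41.8%; 0.072 x 0.582 = 4.2). At R = 39.3% the same step gives 5.1 points.

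Finally, enrolment ended in February 2024, so the size cannot change, and a confidence interval will show the precision achieved. That limits the remedy to wording. It does not make the stated power correct or harmless to interpretation.

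**Conclusion.** The point holds in this form: the 90% is claimed without the two proportions, and the stated inputs do not deliver it when the rate is read as a one-year risk of 50% or 39.3%. This holds for every layout in the table at the plan's own ICC. Within the ceiling of 60 hospitals a year, power is at most about a third at 50%, and a little over a half at 39.3%.

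It rests on three assumptions: the 80% is absolute risk, as worded; patients spared infection have the risk of uninfected patients; and the rate covers a full year. Only the third is seriously open, and the protocol could settle it in one sentence. What effect was actually entered in the software cannot be told from the document. The planned Wilcoxon test on cluster rates would lower power slightly further.

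**What to change.** In the Sample size section:

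1. Derive the effect as difference in infection x (risk if infected - risk if not infected).
2. State how 50 per 100 person-years was turned into a proportion, including the time at risk assumed.
3. Give the resulting control and intervention proportions. These are about 50.0% v 47.5% if 50% is the one-year risk, and should not be fixed at those values if another conversion was used.
4. Restate power, and the difference detectable with 90% power, for the hospital-seasons actually enrolled.

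In the Discussion, qualify or remove the statement about power unless the restated figure supports it.

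The cost is rewording one paragraph and one sentence. No patients, procedures or analyses change. Unless a short time at risk was intended and can be justified, the price is a less favourable stated power.

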## Assignment of interventions: allocation

### Sequence generation, concealment, and implementation {16a,16b,16c}

Computer-generated random numbers are used to assign participating hospitals to the intervention or control group in a 1:1 ratio. Randomization is stratified by province to ensure the numbers of intervention and control hospitals are balanced.

Given the characteristic of the intervention, it will be impossible for the study investigator or the physicians to be blinded to the group allocation. The assignment of either intervention or control will be communicated to site investigators. However, the investigators at each site are blind to the sequence generation, thus ensuring that they have no opportunity to anticipate the allocation of their site until the study group assignment is revealed. In the second and the third influenza season, participating hospitals are re-randomized using the same process before the planned recruitment window.

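### The stated 90% power does not follow from the plan's own inputs for 122 clusters of 50 at a control risk of 39–50%, and the control risk itself is not defined

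*Protocol article*

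**What the plan says.** All the inputs are in Sample size {14} unless noted.

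- Control outcome: the one-year rate of death or readmission "is 50 per 100 person-years, after events in the non-influenza season or within 30 days of hospital discharge are excluded".
- Method: PASS 2020, "test for two proportions in a cluster randomized design".
- Effect: "A influenza infection rate of 15% in the background population"; 80% of infected patients have the primary endpoint; vaccine protection is 60%; uptake is 90% in the intervention arm and 10% in the control arm.
- Loss to follow-up is 10%, and the intra-class correlation "at participating hospitals was 0.03".
- Size: "A sample size of 122 hospitals participating over 3 influenza seasons in which 50 patients are recruited per hospital each season".
- Claimed result: the section says that a trial of this size "would provide 90% power at a two-tailed significance level of < 0.05".

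Allocation is to "assign participating hospitals to the intervention or control group in a 1:1 ratio", and hospitals are randomized again before each season. Trial design {8} says that the size was adjusted for 10% uptake in controls. Outcomes {12} defines the endpoint as all-cause and counts only in-season events after day 30. The Discussion describes the study as well powered.

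**The concern.** A two-proportion method needs the share of patients with an event in each arm. The plan gives a rate per person-time, no time at risk and no conversion, so the reader cannot tell which control risk stands behind the 90%. The effect is stated as a chain of probabilities, and the product of that chain is smaller than the difference that best reproduces 122 hospitals.

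The chain also leaves something out. A patient spared influenza still has the background risk of death or admission, because the endpoint is all-cause. Unless the 80% means influenza-attributable risk, that background has to be subtracted, and its size depends on the undefined control risk.

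What is at stake is how a neutral result is read. If true power is nearer 80%, or much lower, a neutral finding says less against the vaccine than the stated 90% implies.

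**Working it through.** **Formulas.** With 61 clusters per arm, m patients per cluster and ICC 0.03, the design effect is 1 + (m − 1) × 0.03 and the effective number per arm is n = 61m / design effect.

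- m = 50: 3,050 / 2.47 = 1,234.8
- m = 45 (10% lost): 2,745 / 2.32 = 1,183.2

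Power = Φ(Δ / √[(p0(1 − p0) + p1(1 − p1)) / n] − 1.96). Pooling the variance under the null changes this by about 0.1 point at most.

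**Difference from the stated chain.**

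- With 10% control uptake: 0.15 × 0.80 × 0.60 × (0.90 − 0.10) = 0.0576
- With zero control uptake: 0.15 × 0.80 × 0.60 × 0.90 = 0.0648

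**Reproducing the plan's figure.** Take p0 = 0.50, Δ = 0.0648 and m = 50. The standard error is √(0.4958 / 1,234.8) = 0.02004, so 0.0648 / 0.02004 − 1.96 = 1.27 and power is 89.9%. The requirement for 90% is 122.9 clusters. This is the closest match, and it leaves out both control uptake and loss.

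**With the stated control uptake.** Take p0 = 0.50, Δ = 0.0576 and m = 50. The standard error is √(0.4967 / 1,234.8) = 0.02006, so 0.0576 / 0.02006 − 1.96 = 0.91 and power is 81.9%.

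**Control risk implied by the rate**, if it is a constant first-event rate.

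- Full year: 1 − exp(−0.5) = 0.393
- Eligible season only (assumption: 155 days): 1 − exp(−0.5 × 155/365) = 0.191

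| Control risk | Difference (points) | Power, m = 50 | Power, m = 45 |
|---|---|---|---|
| 50% | 6.48 | 89.9% | 88.6% |
| 39.3% | 6.48 | 91.9% | 90.8% |
| 50% | 5.76 | 81.9% | 80.3% |
| 39.3% | 5.76 | 84.6% | 83.0% |
| 19.1% | 5.76 | 97.3% | 96.8% |

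At 5.76 points, 90% power needs about 156 to 163 clusters at a 50% control risk and 145 to 151 at 39.3%.

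**If the 80% is total risk among the infected.**

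- Infected, control: 0.15 × (1 − 0.60 × 0.10) = 0.141
- Infected, intervention: 0.15 × (1 − 0.60 × 0.90) = 0.069
- Infections prevented: 0.141 − 0.069 = 0.072
- Uninfected risk u = (p0 − 0.141 × 0.80) / 0.859
- Net difference = 0.072 × (0.80 − u)

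| Control risk | u | Net difference (points) | Power, m = 45 |
|---|---|---|---|
| 50% | 0.451 | 2.5 | 23% |
| 39.3% | 0.327 | 3.4 | 40% |
| 19.1% | 0.091 | 5.1 | 92% |

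**The case against.** A reader might infer that 50 per 100 person-years was mistakenly entered as 50%, and that this slip inflates the power. The documents support neither step. The proportion entered is never stated. A 50% control risk fits best, but 39.3% with 6.48 points and m = 45 also gives about 91% power and 119 clusters. The figure may also loosely mean 50 per 100 patients, in which case 50% is right. And conversion on its own raises power by 2 to 3 points.

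A second tempting inference is that the 90% is simply false and should be struck out. That goes too far. If the rate applies only to in-season time after day 30, which is closest to the endpoint definition, the control risk is near 19% and power is 92–97%. If the 80% is read as attributable risk, 5.76 points stands whatever the control risk.

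The size can also be read as 122 hospitals with 150 patients each. With 5.76 points and a 50% control risk, that gives about 91–92% power even after loss. But it calls for 115 to 117 hospitals, not 122. It also sits badly with randomization afresh each season and with Study setting {9}, which allows up to 60 hospitals a year: 122 hospitals over three seasons is 366 hospital-seasons, against a ceiling of 3 × 60 = 180. The hospital-season reading fits the design better, but the text does not settle it.

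These points stand as reasons to ask for the inputs. None of them derives the printed 122 and 90% from the stated assumptions.

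**Conclusion.** The concern holds in a limited form. For 122 clusters of 50, with ICC 0.03 and the stated 10% control uptake, power is 80–82% at a 50% control risk and 83–85% at 39.3%, against the stated 90%. The shortfall comes from the difference between arms, and the best reproduction of the plan's figure conflicts with the adjustment claimed in Trial design {8}.

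The undefined control risk matters because it decides how large the net effect can be. If the 80% is total risk, as worded, power runs from 23% at a 50% control risk to 92% at about 19%. These figures assume a constant first-event rate, loss handled as 45 evaluable patients per cluster, and 155 eligible days for the lowest risk. They do not show that the trial is underpowered. They show that the 90% is not supported as written.

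**What to change.** In Sample size {14}, state:

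1. the expected cumulative proportion of control patients with a primary event, and the time at risk it covers;
2. whether the 80% is the total endpoint risk among infected patients or the influenza-attributable part;
3. whether a cluster is a hospital or a hospital-season, and its size;
4. both arms' proportions, with 10% control uptake and 10% loss included.

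Then replace the 90% by the power recomputed from these inputs, and keep the Discussion's description of the study as well powered only if that figure supports it.

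Enrollment has closed (Trial status), so this changes text only and needs no further patients. The cost is that the restated power may be less favourable.
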